**Retrieval process time points.**

#### Primary outcome measure

Stabilisation time (*ST*). Clinical time spent by the retrieval team with at the bedside at the referring hospital (*ST* = *time*_*t*3_ − *time*_*t*2_). We will analyse all participants after stratifying for initial risk, as measured using the Paediatric Index of Mortality 3 (PIM3) [14].

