#### Secondary outcome measures

Child’s physiological status using repeated measure scored using the Children’s Emergency Warning Tool (CEWT) (Authors: Royal Children’s Hospital, Queensland Health, unpublished) at two time points: (1) at time of initial call from the referring hospital (*CEWT*_*t*0_); and (2) at time of arrival of the retrieving team at the bedside at the referring hospital (*CEWT*_*t*2_).CEWT is an observation-chart based tool used within hospitals in Queensland. The tool is designed to identify patient deterioration and to trigger appropriate clinical escalations. The tool has nine components: respiratory rate, respiratory distress, Oxygen rate, Oxygen saturation, temperature, heart rate, blood pressure, capillary refill time, and level of consciousness. Observations are charted at the bedside, as with a conventional patient chart. Within each component, observations are translated to a score, on a scale of 1 (best) to 3 (worst). A score of ‘E’ and purple colour coding is used to prompt an emergency response (e.g. a respiratory rate <10 breaths/min, heart rate <60 beats/min or any component of blood pressure <50 mmHg).After each patient assessment, a total CEWT score is calculated by summing the component scores. A range of clinical responses are triggered by both significant negative changes in between-assessment component scores, and by the total CEWT score.Change in diagnosis (*DX*) using repeated measure taken at three time points: (1) at time of initial call to RSQ (*DX*_*t*0_); (2) at time of arrival of the retrieval team at the bedside at the referring hospital (*DX*_*t*2_); and (3) at time of arrival of the retrieval team and retrieved patient back at the PICU (*DX*_*t*5_).Destination of retrieved patients at the tertiary hospital (i.e. general ward vs. PICU).Retrieval decision (retrieval conducted/not conducted)PICU LoS for retrieved patients.

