### Data collection

This study will use routinely collected patient care and health service reporting data. Sources will be: (1) the retrieval form, for clinical and timing information relating to the retrieval mission; (2) the patient chart, for diagnosis information and admission location at the tertiary hospital. For cases in the intervention arm, the audio and video of all consultations will be recorded to allow retrospective analysis. An activity log will be maintained to provide summary statistics of telemedicine and telephone usage during the study period.

Economic data routinely collected will include hospital admission data, length of stay by ward type, procedures, and Diagnostic Related Groups (DRGs). Additional data to be collected during the trial will include staffing, resource use and costs for the intervention, and the distance travelled by patients and their families. References for economic analyses will be: (1) The National Hospital Cost Data Collection Cost Report Round 14 (2009–2010) [25]; (2) current transport costs (sourced from emergency transport providers) and current (3) Queensland Health salary scales for staff costs.

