**Table 2 Tab2:** **Statistical analyses for each outcome measure**

**Outcome measure**		**Statistical Method**
P1	Stabilisation time^1^	Linear regression with stabilisation time as the outcome, type of consultation as the main effect and PIM3 score as a co-variable
S1	Change in patient’s physiological status	Linear mixed effects model with physiological status as outcome, type of consultation and time as main effects, and a consultation-by-time interaction term.
S2	Change in diagnosis	Logistic mixed effects model with diagnosis as outcome, type of consultation and time as main effects, and a consultation-by-time interaction term.
S3	Destination of retrieved patients	Logistic regression with destination as outcome and type of consultation as the main effect.
S4	Retrieval decision	Logistic regression with retrieval decision as outcome and type of consultation as the main effect.
S5	PICU LoS^1^	Linear regression with LoS as the outcome, and type of consultation as the main effect.

^1^Data relating to stabilisation time and PICU LoS will transformed if necessary to meet assumptions of regression model.

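### Table 2 adjusts stabilisation time for initial risk but analyses PICU length of stay (S5) and destination (S3) by arm alone, forgoing efficiency that a planned baseline severity score could give

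*Protocol article*

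**What the plan says.** The Data analysis section refers to Table 2 for the method for each outcome, so the table fixes the models outcome by outcome.

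- P1, stabilisation time: "type of consultation as the main effect and PIM3 score as a co-variable". The Primary outcome measure section gives the same intention: "We will analyse all participants after stratifying for initial risk, as measured using the Paediatric Index of Mortality 3 (PIM3").
- S3, destination: "Logistic regression with destination as outcome and type of consultation as the main effect", with no risk term.
- S4, whether the child is retrieved: "Logistic regression with retrieval decision as outcome and type of consultation as the main effect", again with no risk term.
- S5, PICU length of stay: "Linear regression with LoS as the outcome, and type of consultation as the main effect". A footnote allows length of stay to be transformed.

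The Secondary outcome measures section limits S5 to retrieved children ("PICU LoS for retrieved patients") and S3 likewise. The same section plans a CEWT score "at time of initial call from the referring hospital", labelled t0. The article gives no reason for including initial risk in P1 and leaving it out of S3 and S5.

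**The concern.** Length of stay in PICU, and whether a retrieved child goes to PICU or to a ward, plausibly depend on how sick the child was at the call. P1 already needs PIM3 for retrieved children, and these are the children analysed in S3 and S5. According to the Randomisation section, allocation is blocked within site, with no severity stratum. Severity-related variation in length of stay therefore stays in the residual of the S5 model, and its confidence interval is wider than the planned data would allow.

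The Hypotheses section names both outcomes, and length of stay and tertiary admissions also carry the economic hypothesis. The Sample size section says that resources fix the number of sites and the duration, so the trial cannot easily gain information by recruiting more children.

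**Working it through.** **Inputs.** From the Sample size section: 80 children per arm (160 in total), SD of stabilisation time 41 minutes, alpha 0.05 (taken as two-sided), difference 18 minutes, power 80%. The article gives no power figure for S3 or S5 and no correlation between a severity score and any outcome. R², the share of outcome variance that the score explains, is therefore assumed and shown as a range.

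**The plan's own figure.** The SE of the difference is 41 × √(2/80) = 6.48 minutes. Power = Φ(18/6.48 − 1.96) = 79.3%, which agrees with the stated 80%. This figure concerns P1 and does not depend on the point made here.

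**S5, linear model.** Adjustment multiplies the SE by √(1 − R²). Take an effect with 80% power unadjusted, which at 80 per arm is (1.96 + 0.842) × √(2/80) = 0.443 SD. Then adjusted power = Φ(2.802/√(1 − R²) − 1.96), and the equivalent unadjusted total is 160/(1 − R²).

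| Assumed R² | Change in SE | Power | Equivalent unadjusted N |
|---|---|---|---|
| 0.02 | −1.0% | 80.8% | 163 |
| 0.05 | −2.5% | 82.0% | 168 |
| 0.10 | −5.1% | 84.0% | 178 |
| 0.20 | −10.6% | 87.9% | 200 |
| 0.30 | −16.3% | 91.8% | 229 |

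S5 covers retrieved children only, so fewer than 80 per arm may be analysed. With 60 per arm, for illustration, the effect with 80% power becomes 0.511 SD. The power column is unchanged and the equivalent N runs from 122 to 171.

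**S3, logistic model.** I simulated 160 children, 1,500 runs per setting, with an assumed conditional log odds ratio of −1.0 for arm and an intercept of −0.8.

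| Assumed log odds ratio per SD of severity | Power, unadjusted → adjusted | SE of log odds ratio, unadjusted → adjusted | Mean log odds ratio, unadjusted → adjusted |
|---|---|---|---|
| 0.5 | 69.5% → 72.3% | 0.401 → 0.413 | −0.978 → −1.025 |
| 1.0 | 62.7% → 70.3% | 0.381 → 0.421 | −0.863 → −1.027 |
| 1.5 | 54.5% → 65.7% | 0.363 → 0.439 | −0.741 → −1.028 |

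Power rises by about 3 to 11 points. The SE also rises, because the adjusted odds ratio is conditional on severity and lies further from the null than the marginal one.

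**Timing of the scores.** The Patient recruitment section has the referring hospital call the retrieval service first. The PICU consultant is contacted next and then applies the randomisation. CEWT at t0 belongs to that first call, so it refers to a time before allocation. No scoring time is given for PIM3.

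**The case against.** The strongest reply is that an arm-only model is a legitimate choice under randomisation and that Table 2 agrees with the rest of the article, which ties PIM3 to the primary outcome only. That stands: there is no contradiction, and this is a matter of efficiency in secondary outcomes. The size of the gain is also unknown. At R² = 0.02 it is under one power point.

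A reader might infer more than the article supports, in four ways.

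- *That chance severity imbalance biases the unadjusted results.* With 80 per arm, a standardised imbalance above 0.2 SD in either direction has a probability of about 21% (SE √(2/80) = 0.158). The unadjusted standard error already reflects this, so it is not an additional bias.
- *That precision is lost in the logistic rows.* The simulation shows the SE of the log odds ratio rising with adjustment. Only power improves, and the estimand changes.
- *That the data for S4 are in hand.* The article does not say that PIM3 or CEWT at t0 is recorded for children who are not retrieved. The Data collection section names "the retrieval form, for clinical and timing information relating to the retrieval mission" and the patient chart for diagnosis and admission location. The unadjusted S4 comparison covers all randomised children and is valid.
- *That the Economic analysis section shows large severity-related variation.* It says that PICU costs are skewed by some very long stays. It does not attribute these to initial severity.

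One further caution stands. If PIM3 were scored on values from after the consultation, adjusting for it could remove part of the effect under study, since the consultation is hypothesised to improve the child's condition before the team arrives.

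**Conclusion.** The point holds as a low-cost improvement, chiefly for S5. Leaving S3 and S5 unadjusted is not an error. For S5, the efficiency forgone is about 1 to 12 power points from an 80% base, if a baseline severity score explains 2% to 30% of the variance in length of stay on the scale analysed. For S3, the gain is about 3 to 11 power points under the assumed prognostic strengths, with no reduction in the SE of the log odds ratio. All these figures rest on assumed associations.

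S3 and S5 are restricted to retrieved children, and retrieval is itself an outcome (S4), so case mix may differ between arms. Severity adjustment reduces that selection but cannot remove it. For S4 the case depends on data whose availability the article does not show.

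**What to change.** In Table 2, add one pre-randomisation severity covariate to S5 and S3: PIM3 if it is scored on values from before the randomised consultation, otherwise CEWT at t0. State the scoring time. Report the unadjusted results alongside. For S3, also report a risk difference standardised over the analysed children, because the adjusted odds ratio is conditional on severity.

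Extend this to S4 only once it is confirmed that CEWT at t0 is recorded for every randomised child, retrieved or not. Note with the S3 and S5 results that adjustment does not remove the selection into the retrieved group.

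The cost is one degree of freedom per model and, for S3, one extra reported quantity. Deciding this in advance also avoids a post hoc choice if severity turns out to be imbalanced.

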### Economic analysis

A cost-minimisation analysis will be undertaken. Resource use collected during the trial will be costed with unit costs applied to each resource to derive the cost per case. Costs per day stay in PICU and other hospital wards will be estimated on a *per diem* basis to more accurately estimate total hospital costs for this group of patients (PICU costs are typically skewed due to some cases having very long stays with exceptionally high costs).

All cost data will be standardised to current values. No discounting will be necessary due to the short time horizon (<12 months) for the analysis. The group with the lowest costs will be deemed as the optimal strategy. One way deterministic sensitivity analysis will be undertaken to identify factors affecting the stability of the results.

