### Randomisation

Generation of intervention/control arm allocation sequences will occur centrally. Sequences will be generated using permuted block randomisation, with random block sizes of 6,8 or 10 entries and a 1:1 allocation ratio using an online true random number generation service [19]. The process of generating these sequences will be conducted by an independent party. Four tables of random numbers will be generated, one for each study site. Odd numbers will denote allocation to the control arm and even numbers to the intervention. The tables will be held securely on a server on a private network.

A password-protected custom application (accessible by computer or portable device), driven by the random number tables, will be provided for the PICU clinicians to determine cases and controls at time of initial retrieval call from RSQ. The application will record all accesses and allocations.

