### Sample size

In this study, resources limit the number of study sites to four and the study duration to 24 months. It is estimated that during the study period there will be 200 retrieval calls relating to eligible participants. We estimate an 80% participation rate (20% attrition due to lack of consent or clinicians electing not to consult by telemedicine and continuing by telephone) and consequently estimate the study will recruit a total of 160 retrieval participants with 80 in each arm. Retrospective stabilisation time data for the study sites showed a standard deviation of 41 minutes. With alpha = 0.05 we have 80% power to detect a clinically important difference in stabilisation time between-consultation types of 18 minutes or greater.

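### The economic analysis calls the cheaper arm optimal without any condition on the clinical results, although the trial is built to show that outcomes differ

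*Protocol article*

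**What the plan says.** In the protocol article, the Economic analysis section names the method: "A cost-minimisation analysis will be undertaken". It then gives the decision rule: "The group with the lowest costs will be deemed as the optimal strategy". It attaches no condition on the clinical outcomes, no equivalence margin and no interval or test. The same section remarks that "PICU costs are typically skewed due to some cases having very long stays with exceptionally high costs". The uncertainty analysis it states is this: "One way deterministic sensitivity analysis will be undertaken to identify factors affecting the stability of the results".

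The section Objectives and hypotheses predicts that telemedicine will shorten stabilisation, improve the child's condition by the time the team arrives, reduce diagnostic discordance, reduce ward admissions among retrieved children and shorten PICU stay. Its economic hypothesis is one of savings to the health service through fewer retrievals, fewer unnecessary tertiary admissions and shorter stays. The Sample size section is framed for superiority: "With alpha = 0.05 we have 80% power to detect a clinically important difference in stabilisation time between-consultation types of 18 minutes or greater".

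**The concern.** Choosing between strategies on cost alone is justified when their outcomes can be taken as equal. Here the method is fixed in advance, in a trial whose purpose is to show that outcomes differ. Nothing in the rule links the economic conclusion to what the clinical analyses find.

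Two things are at stake. First, if telemedicine achieves its clinical aims but costs a little more, the rule calls the telephone optimal. That is a policy statement which the clinical results in the same report would not support. Second, the rule picks the lower of two observed costs however close they are. Barring an exact tie it names a winner every time, including when the data cannot separate the arms. The Discussion addresses the results to policy makers, and they are the readers most likely to take the word optimal at face value.

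**Working it through.** **1. Is the trial sized for superiority?** Inputs from Sample size and Randomisation: SD 41 minutes ("Retrospective stabilisation time data for the study sites showed a standard deviation of 41 minutes"), 80 per arm ("estimate the study will recruit a total of 160 retrieval participants with 80 in each arm"), difference 18 minutes, alpha 0.05 (two-sided assumed) and a "1:1 allocation ratio".

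- Standard error of the difference = 41 × √(2/80) = 6.48 minutes.
- Power = Φ(18/6.48 − 1.96) = Φ(0.82) = 79.3%, against 80% stated.
- Smallest difference detectable with 80% power = (1.96 + 0.84) × 6.48 = 18.2 minutes.

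The plan's figure reproduces with a two-sided test (one-sided power would be 87.1%). The design is a superiority design for a difference that the article itself calls clinically important. It was not sized to show the equality that cost-minimisation presumes.

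**2. Which hypothesised effects reach the cost comparison?** This sets Objectives and hypotheses beside Data collection and Economic analysis.

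- Number of retrievals, tertiary admissions, ward type and length of stay: yes, as resource use.
- Stabilisation time: at most in part, as staff time.
- Physiological status (CEWT) and diagnostic concordance: no.

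The last item, and whatever value shorter stabilisation has beyond staff cost, cannot influence which arm is called optimal.

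**3. What does the rule do with sampling error?** The article gives no mean or SD of cost. I assume a coefficient of variation (CV = SD/mean) of 1 to 2, 80 per arm and a true cost difference of 10% of the mean.

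- Relative standard error of the cost difference = CV × √(2/80).
- 95% half-width = 1.96 × that standard error.
- Probability of naming the truly dearer arm = Φ(−0.10 / standard error).

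| Assumed CV | Relative SE | 95% half-width, % of mean cost | P(names dearer arm) |
|---|---|---|---|
| 1.0 | 0.158 | 31% | 26% |
| 1.5 | 0.237 | 46% | 34% |
| 2.0 | 0.316 | 62% | 38% |

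A simulation with lognormal costs (100,000 replicates, 80 per arm) gives 25%, 32% and 36% for the same three CVs, so the normal approximation is adequate. With a true 20% difference the simulated figures fall to 8%, 16% and 22%. With equal true costs each arm is named about half the time.

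**4. The two parts together.** Suppose telemedicine is truly 18 minutes better at equal true cost. If the cost estimate is independent of the clinical gain, the rule names the telephone arm about half the time. If telemedicine truly costs more, it does so more often.

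**5. Does the stated sensitivity analysis cover this?** No. A one-way deterministic analysis changes one input at a time, such as a unit cost. It shows how the answer depends on assumptions, not how much it would vary with another sample of children. Per-diem costing does not remove the variation either, because length of stay still differs between children.

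**The case against.** The strongest reply has four parts.

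*The economic hypothesis is itself about cost.* This largely stands. A reader might infer that the rule ignores the expected clinical benefit altogether. The article does not support that, because retrievals, admissions and length of stay are counted as costs and the Discussion describes the aim as costing the observed effects. What remains outside is narrower: physiological status, diagnosis and the non-monetary value of shorter stabilisation.

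*The economic analysis is secondary.* This stands. Table 2 analyses each clinical outcome separately by type of consultation. The rule touches neither allocation, the primary analysis nor the sample size, so it would be wrong to infer that the trial's clinical conclusions are at risk.

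*A confidence interval for cost could sit in a fuller plan.* This stands too. The article does not say that costs will be reported without an interval, so its absence is not the finding. But the decision sentence is explicit, and a fuller plan would have to override it.

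*If true costs are equal, picking either arm loses nothing in cost.* This is correct, and it means that naming a winner by chance does harm mainly when the clinical effects differ. It does not excuse presenting an arbitrary choice as the optimal strategy.

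The percentages in the table rest on my assumed CV and true difference, and should not be read as figures from the article.

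**Conclusion.** Wrong as written, and a should-fix. The article commits to cost-minimisation and to an unconditional lowest-cost rule, in a trial that hypothesises, and is powered for, better outcomes with telemedicine. Followed literally, the rule can name the clinically worse arm optimal, and it takes no account of sampling error.

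The conflict between method and hypotheses, and the fact that the rule always yields a winner, follow from the text with no outside assumption. The size of the sampling-error problem does depend on assumptions: with a cost CV of 1 to 2, 80 per arm and a true 10% difference, the dearer arm is named in about 26% to 38% of trials. A smaller CV or a larger true difference would lower that range.

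**What to change.** Delete the lowest-cost sentence and replace cost-minimisation with a cost-consequence analysis. By randomised arm and over all randomised children, report the mean incremental cost with a bootstrap 95% confidence interval. Set it beside the differences in stabilisation time, CEWT, diagnosis, destination, retrieval decision and PICU length of stay. Keep the one-way sensitivity analysis for unit costs.

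It may be tempting to retain cost-minimisation on condition that the interval for stabilisation time lies within ±18 minutes. I would not do this. It tests one outcome and leaves physiological status and diagnosis unchecked. Stabilisation time exists only for retrieved children, whereas costs cover all who are randomised. It also takes the full superiority difference as an equivalence margin.

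The cost is a few lines of protocol text and a bootstrap on patient-level resource data that Data collection already plans to gather. No extra participants or measurements are needed.

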### Objectives and hypotheses

#### Hypotheses

Consultation using real-time video-based telemedicine between a PICU consultant and a referring hospital clinician will:Clinical effectivenessReduce the time needed by the retrieval team to stabilise the child before transportImprove the child’s condition between time of initial call and time of retrieval team arrivalReduce diagnostic discordanceReduce the number of retrieved children being admitted to general wards at the tertiary hospitalReduce PICU LoS for retrieved childrenEconomic effectsFrom the health service perspective, be economically beneficial by reducing the number, and consequently the cost, of (i) retrievals, (ii) unnecessary tertiary hospital admissions, and (iii) LoS.

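### The economic analysis names the cheaper arm optimal whatever the outcomes, although the trial expects outcomes to differ and, apart from cost, records only the retrieval decision for a child who is never retrieved

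*Protocol article*

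**What the plan says.** The Economic analysis section of the protocol article names the method, "A cost-minimisation analysis will be undertaken", and then the decision rule, "The group with the lowest costs will be deemed as the optimal strategy". One-way deterministic sensitivity analysis is planned to look at how stable the result is. The horizon is short: "No discounting will be necessary due to the short time horizon (<12 months) for the analysis".

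The Hypotheses section predicts five clinical differences between telemedicine and telephone. Separately, under economic effects and from the health service perspective, it predicts that telemedicine will "be economically beneficial by reducing the number, and consequently the cost, of (i) retrievals", as well as fewer unnecessary tertiary admissions and shorter stays.

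The outcome list (Primary outcome measure, Secondary outcome measures, Table 2) has six entries. The retrieval decision is one of them, analysed by "Logistic regression with retrieval decision as outcome and type of consultation as the main effect". Data collection adds economic data: admissions, stays by type of ward, procedures and DRGs.

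**The concern.** Cost-minimisation compares costs after outcomes have been shown, or can safely be taken, to be equivalent. Here the rule applies whatever the outcomes turn out to be. It can err in either direction: an arm with better clinical results but higher cost would be ranked second, and an arm with worse results but lower cost would be ranked first.

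The second error is the harder one to see in this trial. Fewer retrievals are an expected source of savings, and a child who is not retrieved leaves almost no trace in the clinical outcomes. If a decision not to retrieve was followed by a poor result, the economic verdict would register only the resources used. The article presents its results as useful to health service policy makers, so a label of optimal that rests on cost alone could be carried further than the data allow.

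**Working it through.** **Step 1. Is equivalence assumed or tested?** The Hypotheses section predicts shorter stabilisation, a better condition at team arrival, less diagnostic discordance, fewer ward admissions among retrieved children and shorter PICU stay. Each is a predicted difference. The Sample size section powers a difference, and its figure reproduces. With SD 41 and 80 per arm, the standard error is 41 × √(2/80) = 6.48 minutes. Two-sided power for 18 minutes is then Φ(18/6.48 − 1.96) = Φ(0.82) = 79%, against the stated 80%. This calculation concerns superiority on one outcome. No equivalence margin is stated anywhere in the article.

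**Step 2. Which outcomes exist for a child who is never retrieved?**

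| Outcome | What it needs | Never-retrieved child |
|---|---|---|
| P1 stabilisation time | "Clinical time spent by the retrieval team with at the bedside at the referring hospital" | none |
| S1 CEWT change | second score "at time of arrival of the retrieving team at the bedside at the referring hospital" | initial score only |
| S2 diagnosis | later points at team arrival and on return to the PICU | initial diagnosis only |
| S3 destination | retrieved patients | none |
| S4 retrieval decision | the decision | recorded |
| S5 PICU LoS | retrieved patients | none |

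PIM3 enters only as an adjustment for initial risk. After the initial call, S4 and the costs are all that the listed measures hold for this child. S4 is a two-level variable and cannot separate a retrieval safely avoided from one whose absence did harm, although the Discussion says that the appropriateness of retrieval will be examined.

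**Step 3. How can harm reach the economic verdict?** Two routes follow from Data collection and Economic analysis:

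- Deterioration followed by a longer stay, a later retrieval or a PICU admission adds cost, provided the admission data cover that stay. The verdict then moves against the arm.
- Death soon after the call, without escalation, uses few resources. The verdict then moves in favour of the arm.

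The sign depends on resource use, not on the child's outcome.

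**Step 4. Could the trial show equal safety?** The article gives no event rates, so these are assumptions. Two-sided power at 80 per arm, alpha 0.05, is Φ{(|p₂ − p₁| − 1.96√(2p̄(1 − p̄)/80)) / √((p₁(1 − p₁) + p₂(1 − p₂))/80)}:

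| Assumed risks | Power |
|---|---|
| 2% v 5% | 18% |
| 2% v 8% | 41% |
| 5% v 10% | 22% |
| 5% v 15% | 56% |

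With equal true risks, the approximate half-width of the 95% interval for a risk difference is 1.96√(2p(1 − p)/80). This gives 4.3, 6.8 and 9.3 percentage points at risks of 2%, 5% and 10%. Such outcomes can be described but cannot establish equivalence.

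**Step 5. Could the verdict depend on the direction of these events?** For two independent binomial counts with n = 80 and the same risk, the chance that the telemedicine arm has strictly more events is 32%, 38%, 43% and 45% at risks of 1%, 2%, 5% and 10%. A rule based on direction would often be decided by luck.

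**The case against.** Several stronger readings are tempting, and the article does not support them.

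- A reader might infer that a non-retrieved child can only lower the arm's cost. That is too strong: admissions and stays by ward type are costed over a horizon of under 12 months, so deterioration with later care can raise it.
- A reader might extend the point to delayed retrieval. A child retrieved late is still retrieved, has a CEWT score at team arrival and contributes to the other outcomes. Deterioration during the wait is what S1 measures.
- A reader might say that S4 itself would report under-retrieval as a benefit. S4 is an undirected comparison. Fewer retrievals are called beneficial only among the economic effects, so the risk is confined to the economic conclusion, and to cases where savings exceed later costs.
- A reader might size the problem by the upper limit for zero deaths in 80, 1 − 0.05^(1/80) = 3.7%. The arithmetic is right, but it describes any arm of 80. The relevant quantity is the number of children not retrieved, which the article does not give. The power calculation uses all 80 per arm for stabilisation time, which suggests that few were expected.
- Safety monitoring and routine reporting of deaths may stand in a full protocol that is not shown. Their absence from an article is not a fault.

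What remains is the rule itself. It is stated without qualification and conflicts with the article's own hypotheses, and safety monitoring elsewhere would not alter it.

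**Conclusion.** The point holds in a limited form. The article pairs cost-minimisation with an unconditional lowest-cost rule, in a trial that predicts different outcomes and cannot show equivalence. Followed as written, the rule can give the wrong economic verdict. This could happen where clinical outcomes differ between arms, and where a child who was never retrieved came to harm at little cost.

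How often the second case would arise cannot be calculated from the article. It requires that some randomised children are never retrieved, that harm follows in some of them, and that the savings exceed any later costs. The documents do not show that telemedicine would cause under-retrieval, and the primary analysis of stabilisation time does not use this rule. The power and interval figures above rest on assumed risks and serve only to show that equal safety could not be demonstrated at this size. The change should be made because it is cheap and the rule is explicit.

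**What to change.** In the Economic analysis section:

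1. Delete the rule that deems the lowest-cost group optimal, and replace cost-minimisation with a cost-consequence analysis.
2. Present the between-arm cost difference with its 95% interval beside the trial's clinical outcomes.
3. For every randomised child, retrieved or not, add by arm (a) death before discharge and (b) later retrieval or PICU admission after a decision not to retrieve. Report both as descriptive risk differences with 95% intervals, next to S4.
4. State that a lower cost alone does not establish the preferable strategy. Do not make the conclusion depend on which arm has more of a few rare events.

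The sample size and the primary analysis are unchanged. The cost is a short extra extraction: Data collection does not list discharge status, and it should be confirmed that admission data cover the referring hospitals for children who stay there. The intervals will be wide and the economic conclusion will be worded more cautiously.
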